## Abstract

**Background:**

First-pass stress-perfusion cardiovascular magnetic resonance (CMR) imaging is the guidelines-recommended non-invasive test for the detection of obstructive coronary artery disease (CAD). Recently developed quantitative perfusion CMR (QP CMR) allows quantification of myocardial blood flow. Moreover, the latest developments established several methods of CAD assessment without the need for a contrast agent, including stress T1 mapping reactivity (∆T1) and oxygenation-sensitive CMR (OS-CMR). These methods might eliminate the need for contrast administration in clinical practice, reducing time, invasiveness, and costs, thereby simplifying the evaluation of patients with suspected obstructive CAD. The ADVOCATE-CMR study aims to validate QP CMR, ∆T1, and OS-CMR imaging against invasive fractional flow reserve (FFR) for the detection of obstructive CAD. The study also aims to head-to-head compare the diagnostic accuracy of these CMR techniques with the conventional visual assessment of stress-perfusion CMR and to correlate them to short- and long-term clinical outcomes.

**Study design and Methodology:**

ADVOCATE-CMR is a single-center, observational, prospective, cross-sectional cohort study. The study will enroll 182 symptomatic patients with suspected obstructive CAD scheduled for invasive coronary angiography (ICA). Before ICA, all participants will undergo CMR imaging, including OS-CMR with breathing maneuvers, rest, and adenosine stress T1 mapping and rest and adenosine stress first-pass perfusion. Subsequently, ICA will be performed, including FFR, instantaneous wave-free ratio, resting Pd/Pa, coronary flow reserve, and index of microvascular resistance measurements in all main coronary arteries. A follow-up CMR scan with the same protocol will be performed at 3 months after ICA. Clinical follow-up will be performed at 3, 6 months, 1 and 3 years after ICA.

**Conclusion:**

The ADVOCATE-CMR will be the first study comprehensively evaluating and comparing head-to-head the diagnostic performance of a range of contrast- and non-contrast agent-based CMR imaging methods (including QP CMR, ∆T1, and OS-CMR) for the detection of FFR-defined obstructive CAD. We expect to establish a validated and time-efficient diagnostic workflow available to a wide range of general CMR services. Finally, these improvements may enable CMR to become an effective non-invasive, radiation-free gatekeeper for ICA in patients with suspected obstructive CAD, potentially without the need for a contrast agent.

## Background

1

Obstructive coronary artery disease (CAD) involves the formation of atherosclerotic plaques in the lumen of coronary arteries, which causes a demand-supply mismatch of oxygen. Consequently, this leads to myocardial ischemia, reflected by recurrent, transient episodes of chest pain (angina pectoris) [1]. Ischemic heart disease affects around 126 million people worldwide and is the leading global cause of mortality [2], [3], [4]. Early diagnosis of obstructive CAD enables fast initiation of targeted treatment, improves patient quality of life, facilitates rehabilitation, accelerates fast return to the previous socio-economic environment, and reduces costs for society [5], [6].

Invasive coronary angiography (ICA) is regarded as the “gold standard” to detect obstructive CAD, and multiple trials have demonstrated that coronary revascularizations should be ischemia-driven, as measured by fractional flow reserve (FFR), to relieve symptoms and improve outcome [7], [8], [9], [10]. However, despite symptoms, in almost two-thirds of women and one-third of men, ICA does not show obstructive CAD [11], [12], [13]. Therefore, up to 60% of the current diagnostic ICA could be avoided, preventing patients from getting exposed to potential ICA-related risks. Therefore, a reliable non-invasive screening tool to discriminate patients with obstructive CAD from patients without obstructive CAD will prevent unnecessary ICA, thereby reducing costs and increasing efficient use of catheterization laboratories for more targeted procedures. Among others, first-pass stress-perfusion cardiovascular magnetic resonance (CMR) has been proposed as the non-invasive method of choice for the detection of obstructive CAD due to its high spatial resolution, accurate assessment of myocardial viability and function, cost-effectiveness, and lack of ionizing radiation [6], [14], [15], [16], [17], [18], [19]. In clinical routine, first-pass stress-perfusion CMR images are visually analyzed. This approach is based on the evaluation of the arrival and first passage of a gadolinium-based contrast agent (GBCA) through the left ventricular myocardium and the identification of regions with relatively lower signal intensity (SI), indicating hypoperfusion, as a surrogate of myocardial ischemia [20]. However, visual assessment of stress-perfusion CMR may underestimate the extent of perfusion defect in patients with multivessel disease and has poor diagnostic accuracy for the detection of coronary microvascular dysfunction (CMD) [21], [22].

Recently, conventional visual assessment of first-pass perfusion CMR has been substantially improved by quantification of myocardial blood flow (MBF) and the creation of color pixel perfusion maps (quantitative perfusion CMR [QP CMR]) [23], [24], [25], [26], [27], [28], [29], [30], [31]. MBF is quantified by tracer kinetic analysis of the SI curves of GBCA first pass. Until recently, QP CMR required cumbersome and time-consuming manual processing to delineate myocardial regions of interest (ROIs), which made it prone to interobserver variability and prevented its widespread use in clinical routine. To address these limitations, a fully automated, pixel-wise QP CMR image processing framework has been established, which is reproducible, time-efficient, and does not require manual delineation of ROIs and myocardial image segmentation [26]. Fully automated pixel-wise QP CMR has also shown high diagnostic performance for detecting ICA- and/or FFR-confirmed significant CAD [25], [26], [30], [32], [33]. However, QP CMR is still predominantly a research tool due to substantial inter-study differences in acquisition and analysis methods and the lack of established reference standards [34], [35], [36], [37]. Therefore, further research is needed to propose algorithms ready to be used in daily clinical routine in patients with suspected obstructive CAD [32], [38].

However, it must be noted that GBCA-based QP CMR, despite its advantages over the conventional visual assessment approach, is associated with some clinically relevant drawbacks. First-pass perfusion CMR imaging (either conventional or QP) requires administration of GBCA, which for this purpose in most countries is used off-label. In addition, GBCAs are advised not to be used in patients with severe renal dysfunction and have been associated with the rare development of nephrogenic systemic fibrosis. Furthermore, its repeated administration may cause accumulation of gadolinium in brain tissues, albeit of unknown clinical significance [39]. Therefore, there are still some regulations and safety concerns regarding the use of GBCA [40]. Due to these matters, the development and clinical validation of alternative, accurate methods for CMR ischemia detection without the need for GBCA are warranted. Recently, novel, non-GBCA-based CMR imaging strategies have been proposed for evaluation of myocardial ischemia, including stress T1 mapping reactivity (∆T1) and oxygenation-sensitive CMR (OS-CMR). These methods, however, have not been introduced into diagnostics and clinical decision-making in patients with CAD due to the lack of proper validation against the invasive gold standard measures in a real-world population.

Native T1 mapping is a non-contrast agent technique that quantifies the longitudinal relaxation time constant (T1). T1 prolongs in the heart as a result of an increased interstitial space but also because of an increased myocardial free water content. Therefore, T1 mapping may reflect the total myocardial blood volume (MBV) localized in the arteries, capillaries, veins, and myocardium [41], [42], [43], [44]. Obstructive CAD is associated with changes in MBV and therefore, T1 mapping technique has been proposed as a contrast agent-free method to evaluate the presence of hemodynamically significant coronary stenosis. From a pathophysiological point of view, coronary artery stenosis increases vascular resistance, which in intermediate lesions can be compensated by microvascular dilation [45]. In this autoregulatory mechanism, capillaries vasodilate counterbalancing the stenosis severity, which preserves sufficient myocardial perfusion. This vasodilation results in increased stationary MBV and resting native T1 mapping values within the myocardium [44], [45], [46]. Exogenous administration of a vasodilator during stress imaging studies may further dilate microvasculature, and increase MBV and native T1 mapping values. However, in the presence of coronary stenosis, where resting MBV and native T1 values are already high, the difference between rest and stress MBV, thus difference in T1 values (∆T1), will be lower than in normal physiology (Fig. 1). Therefore, measurement of differences in T1 values between vasodilator-induced stress and at rest (∆T1) may identify the degree of MBV increase, which reflects microvascular reserve and the true physiological impact of the stenosis on the downstream coronary circulation [44], [47], [48], [49]. Indeed, several clinical studies have confirmed that ischemic myocardium has higher resting T1 values and blunted ∆T1 (i.e., low difference between already high rest and vasodilator-induced slightly increased T1 values), which is not observed in remote, non-ischemic myocardium (i.e., substantial increase in vasodilator-induced T1 values). Moreover, infarcted myocardial tissue shows even higher resting T1 values in comparison to ischemic myocardium, in the absence of T1 reactivity [47], [49], [50], [51]. Although ∆T1 has been suggested to be a promising non-invasive, non-GBCA-dependent biomarker of myocardial ischemia, its diagnostic accuracy has not been validated against gold standard invasive measures, which prevents its wide clinical adoption.

**Fig. 1 fig0005:**
[figure not shown]
Native T1 mapping and T1 mapping reactivity in normal myocardium, myocardial ischemia, and infarction in rest and vasodilation-induced stress. *ΔT1* stress T1 mapping reactivity

OS-CMR is a technique that non-invasively evaluates myocardial oxygenation without the need for a GBCA. When performed with breathing maneuvers, OS-CMR may become a needle-free, safe, and cost-effective CMR approach for detection of myocardial ischemia. OS-CMR uses the blood-oxygen-level-dependent (BOLD) phenomenon where the deoxygenated hemoglobin acts as an intrinsic paramagnetic contrast agent, enhancing spin-spin interaction, accelerating the transverse magnetization decay, and shortening the spin-spin relaxation times (T2 and T2*) [52], [53]. Therefore, increased levels of deoxygenated hemoglobin within the myocardium lead to shortening of T2* relaxation time, which can be visualized through lower SI in T2*-weighted images or T2* maps [54]. Since myocardial ischemia is directly related to increased levels of deoxygenated hemoglobin in the capillaries, it can be detected as a reduction in SI on OS images. Conversely, an increase in the levels of oxygenated hemoglobin (i.e., decreased amount of deoxygenated hemoglobin) increases SI in the T2*-weighted images (Fig. 2) [54], [55], [56], [57]. Indeed, several relatively small clinical studies have demonstrated that OS-CMR has the potential to effectively detect obstructive CAD [58], [59], [60], [61], [62].

**Fig. 2 fig0010:**
[figure not shown]
Myocardial oxygenation-sensitive signal intensity in normal, ischemic, and infarcted myocardium in rest and stress-induced vasodilation. *B-MORE* breathing-induced myocardial oxygenation reserve, *deOX-Hb* deoxygenated hemoglobin, *SI* signal intensity

For a needle-free diagnostic test for assessing coronary artery function, including the presence of obstructive CAD, OS-CMR has been combined with vasoactive breathing maneuvers, i.e., hyperventilation and breath-hold. These maneuvers lead to differences in blood concentration of CO_2_, which is a potent physiological vasodilator [63]. Accordingly, hyperventilation mildly increases levels of oxygenated hemoglobin but especially decreases capillary CO_2_, which induces vasoconstriction and decreases myocardial SI in OS images. To the contrary, in the absence of CAD, a long breath-hold increases capillary CO_2_, inducing vasodilation, and increasing myocardial SI accordingly (Fig. 2) [64]. Therefore, measurement of the breathing-induced myocardial oxygenation reserve (B-MORE), defined as the relative increase in myocardial oxygenation during a post-hyperventilation breath-hold, or other markers of changes in myocardial oxygenation as observed in OS-CMR images, may serve as an accurate non-invasive biomarker of downstream vascular function. Although OS-CMR with breathing maneuvers as a non-invasive, non-GBCA-based and therefore needle-free method for the detection of coronary vascular dysfunction is promising, it still needs to be properly validated against invasive gold standard measures and other non-invasive imaging modalities before it can be introduced on a wide scale into clinical routine.

The primary objective of ADVOCATE-CMR study is to validate the new, non-invasive QP CMR imaging against invasive gold standard FFR for the detection of obstructive CAD. The main secondary and tertiary objectives are to validate ∆T1 and OS-CMR against FFR for detection of obstructive CAD, to compare (head-to-head) the diagnostic accuracy of the QP CMR, ∆T1, and OS-CMR imaging with the conventional visual assessment of GBCA-based first-pass perfusion imaging to detect obstructive CAD, to correlate these new CMR parameters to short- and long-term clinical outcomes and to study the change in myocardial perfusion, MBV, and myocardial oxygenation after coronary revascularization.

## Methods

2

### Study design

2.1

ADVOCATE-CMR is a single-center, observational, prospective, cross-sectional cohort study performed at the Amsterdam University Medical Centers—Location VUmc. The study is performed in accordance with the principles of the Declaration of Helsinki, and all patients need to provide informed written consent to participate. The study protocol has been approved by the local ethics committee (Medisch Ethische Toetsingscommissie Amsterdam UMC) and is registered in ClinicalTrials.gov under the number NCT06419894.

The flowchart of the study is presented in Fig. 3. The study will enroll 182 symptomatic patients with suspected obstructive CAD scheduled for ICA according to the decision of the treating clinician (see Section 2.9). Before ICA, all study participants will undergo CMR imaging, including rest and adenosine stress perfusion, rest and adenosine stress T1 mapping, and OS-CMR with breathing maneuvers. Subsequently, within 6 weeks, ICA will be performed including FFR, instantaneous wave-free ratio (iFR), resting ratio between proximal and distal coronary pressures over the entire resting cycle period (Pd/Pa), coronary flow reserve (CFR), and index of microvascular resistance (IMR) measurements in all main coronary arteries. A second follow-up CMR scan according to the same scan protocol as the first CMR scan will be performed at 3 months after ICA (or 3 months after revascularization, if performed separately more than 1 day following ICA). Clinical follow-up will be at 3, 6 months, 1 and 3 years after the ICA (or revascularization if applicable).

**Fig. 3 fig0015:**
[figure not shown]
ADVOCATE-CMR study flowchart. *ΔT1* stress T1 mapping reactivity, *CAD* coronary artery disease, *CFR* coronary flow reserve, *CMR* cardiac magnetic resonance, *FFR* fractional flow reserve, *ICA* invasive coronary angiography, *iFR* instantaneous wave-free ratio, *IMR* index of microvascular resistance, *OS* oxygenation-sensitive, *Pd/Pa* ratio between proximal and distal coronary pressures over entire resting cycle period, *QP* quantitative perfusion

### Study endpoints

2.2

Primary, secondary, and tertiary endpoints are presented in Table 1.

**Table 1 tbl0005:** ADVOCATE-CMR study endpoints.

*Primary endpoint*
- Diagnostic accuracy (sensitivity, specificity, accuracy, AUC, PPV, NPV) of QP CMR (stress MBF, stress rMBF, MPR, and rMPR) to detect obstructive CAD, as defined by FFR
*Secondary endpoints*
- Diagnostic accuracy (sensitivity, specificity, accuracy, AUC, PPV, NPV) of ΔT1 to detect obstructive CAD, as defined by FFR - Diagnostic accuracy (sensitivity, specificity, accuracy, AUC, PPV, NPV) of OS-CMR (B-MORE) to detect obstructive CAD, as defined by FFR - Head-to-head comparison of diagnostic accuracies (sensitivity, specificity, accuracy, AUC, PPV, NPV) of QP CMR (stress MBF, stress rMBF, MPR, rMPR), ΔT1, OS-CMR, and conventional visual assessment of GBCA-based first-pass perfusion imaging to detect obstructive CAD, as defined by FFR - Diagnostic accuracy (sensitivity, specificity, accuracy, AUC, PPV, NPV) of QP CMR (stress MBF, stress rMBF, MPR, and rMPR) to detect obstructive CAD, as defined by iFR and resting Pd/Pa - Diagnostic accuracy (sensitivity, specificity, accuracy, AUC, PPV, NPV) of ΔT1 to detect obstructive CAD, as defined by iFR and resting Pd/Pa - Diagnostic accuracy (sensitivity, specificity, accuracy, AUC, PPV, NPV) of OS-CMR (B-MORE) to detect obstructive CAD, as defined by iFR and resting Pd/Pa - Head-to-head comparison of diagnostic accuracies (sensitivity, specificity, accuracy, AUC, PPV, NPV) of QP CMR (stress MBF, stress rMBF, MPR, rMPR), ΔT1, OS-CMR, and conventional visual assessment of GBCA-based first-pass perfusion imaging to detect obstructive CAD, as defined by iFR and resting Pd/Pa - Relation of stress and rest MBF and rMBF, MPR and rMPR, ΔT1 and OS-CMR markers to SAQ-7 Summary score, SAQ-7 Angina Frequency score, SAQ-7 Physical Limitation score, SAQ-7 Quality of Life score (before and after revascularization), and Rose Dyspnea Scale score - Prognostic value of QP CMR (stress MBF, stress rMBF, MPR, and rMPR), stress T1 mapping reactivity and OS-CMR in predicting occurrence of a 1) composite of cardiovascular death, myocardial infarction, ischemia-driven coronary revascularization or stroke; 2) composite of myocardial infarction or ischemia-driven coronary revascularization; 3) composite of cardiovascular death, stroke or myocardial infarction; 4) myocardial infarction; 5) ischemia-driven coronary revascularization; 6) stroke; 7) death from any cause; 8) cardiovascular death
*Tertiary endpoints*
- Diagnostic accuracies (sensitivity, specificity, accuracy, AUC, PPV, NPV) of QP CMR (stress MBF, stress rMBF, MPR, and rMPR), ΔT1, and B-MORE to detect CMD, as defined by CFR - Diagnostic accuracy (sensitivity, specificity, accuracy, AUC, PPV, NPV) of QP CMR (stress MBF, stress rMBF, MPR, and rMPR), ΔT1, and B-MORE to differentiate between CMD (as defined by CFR) and 3-vessel obstructive CAD - Change in stress and rest MBF and rMBF, MPR and rMPR, ΔT1 and B-MORE before and after revascularization - Costs and procedural time of QP CMR, stress T1 mapping reactivity, and OS-CMR compared to ICA

*AUC* area under the curve, *B-MORE* breathing-induced myocardial oxygenation reserve, *CAD* coronary artery disease, *CMD* coronary microvascular dysfunction, *CMR* cardiac magnetic resonance, *FFR* fractional flow reserve, *iFR* instantaneous wave-free ratio, *MBF* myocardial blood flow, *MPR* myocardial perfusion reserve, *NPV* negative predictive value, *OS-CMR* oxygenation-sensitive cardiac magnetic resonance, *Pd/Pa* ratio between proximal and distal coronary pressures over entire resting cycle period, *PPV* positive predictive value, *QP CMR* quantitative perfusion cardiac magnetic resonance, *rMBF* relative myocardial blood flow, *rMPR* relative myocardial perfusion reserve, *SAQ* Seattle Angina Questionnaire, *ΔT1* stress T1 mapping reactivity

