#### Sample size and power calculation

2.9.1

Sample size and power calculation were performed according to the primary endpoint. Based on the literature, we assumed the prevalence of obstructive CAD, as defined by FFR, in the study population to be 45% [72]. A sample with 74 from the positive group and 90 from the negative group achieves an 80% power to detect a difference of 0.09 between the area under the receiver operating characteristics curve (AUC) under the null hypothesis of 0.81 and an AUC under the alternative hypothesis of 0.9, using a two-sided z-test at a significance level of 0.05. The data are continuous responses [30], [72]. The AUC is computed between false positive rates of 0 and 1. The ratio of the standard deviation of the responses in the negative group to the standard deviation of the responses in the positive group is 1. Moreover, a sample of 75 from the positive group and 92 from the negative group achieves 80% power to detect a difference of 0.09 between a diagnostic test with an AUC of 0.81 and another diagnostic test with an AUC of 0.9 using a two-sided z-test at a significance level of 0.05. The correlation between the two diagnostic tests is assumed to be 0.6 for the positive group and 0.6 for the negative group. The drop-out rate in our study has been assumed 10%, which is comparable to other prospective diagnostic studies on stress-perfusion CMR and our previous experience in performing diagnostic studies on non-invasive imaging techniques (including CMR) in the detection of obstructive CAD [73], [74], [75]. Therefore, incorporation of the 10% drop-out to the sample size described above (74 from the positive group and 90 from the negative group, in total 164) results in a total sample size of 182 patients (which should also be sufficient to detect a significant difference between two diagnostic tests as described above).

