#### Statistical analysis

2.9.2

The statistical analysis will be performed using SPSS software package (IBM SPSS Statistics 20.0, Chicago, Illinois) and MedCalc (MedCalc Software 12.7.8.0, Mariakerke, Belgium). For the primary objective of the study, to validate the QP CMR against FFR (similarly for ΔT1 mapping and OS-CMR), first, intraclass correlation coefficients will be calculated, and second, Bland-Altman plots will be constructed. This will be performed for all comparisons between two continuous variables. Moreover, using FFR ≤0.8 as a definition of a hemodynamically significant coronary artery obstruction, AUCs will be determined for prediction of CAD using quantitative measures of QP CMR, ΔT1, and B-MORE, and perfusion defect score for conventional visual assessment of first-pass perfusion stress CMR. AUCs will be compared using the DeLong method. Diagnostic performance measures (sensitivity, specificity, PPV, NPV, and accuracy) will be calculated for the entire cohort, including 95% confidence interval. To prevent overestimation of the sensitivity, specificity, PPV, NPV, and accuracy, a balanced five-fold cross-validation will be performed. Comparison of sensitivity, specificity, and accuracy between different imaging modalities will be performed using McNemar’s test. Results will be considered statistically significant if p-value <0.05.

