## Conclusions and implications

3

The ADVOCATE-CMR study is a single-center, observational, prospective, cross-sectional cohort study to validate QP CMR, ∆T1, and OS-CMR imaging against invasive gold standards (FFR, iFR, or resting Pd/Pa) for the detection of obstructive CAD. This is the first study comprehensively assessing and comparing head-to-head the diagnostic performance of a range of contrast- and non-contrast-based CMR imaging methods for the detection of FFR-defined obstructive CAD. Based on our results, we expect to establish a validated, time-efficient, and cost-effective diagnostic workflow available to a wide range of general CMR services performing CMR. Finally, these improvements may enable CMR to become an effective, potentially needle-free, non-invasive gatekeeper for ICA in patients with suspected obstructive CAD and may become an alternative for conventional invasive, radiation-based strategies.

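### The head-to-head endpoint fixes neither the QP CMR index nor the metric that decides, and an unadjusted p<0.05 puts the chance of a false difference well above 5% on every reading

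*Protocol article*

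**What the plan says.** - **Endpoint.** Table 1 (section 2.2) lists one secondary endpoint that ends with visual assessment: "Head-to-head comparison of diagnostic accuracies (sensitivity, specificity, accuracy, AUC, PPV, NPV) of QP CMR (stress MBF, stress rMBF, MPR, rMPR), ΔT1, OS-CMR, and conventional". That is seven tests on six metrics against FFR. A second entry repeats the list against iFR and resting Pd/Pa.
- **Comparator.** The objectives at the end of the Background give the direction: "to compare (head-to-head) the diagnostic accuracy of the QP CMR, ∆T1, and OS-CMR imaging with the conventional visual assessment". The Abstract says the same in substance.
- **Tests.** Section 2.9.2 states "AUCs will be compared using the DeLong method" and assigns McNemar's test to sensitivity, specificity and accuracy between modalities. So four of the six metrics have a named comparison test.
- **Threshold.** The same section ends with one rule: "Results will be considered statistically significant if p-value <0.05". It mentions no adjustment, order of testing or exploratory status for these comparisons.
- **Power.** Section 2.9.1 sizes the study on a single-AUC test (74 positive, 90 negative). It adds that 75 positive and 92 negative "achieves 80% power to detect a difference of 0.09 between a diagnostic test with an AUC of 0.81 and another diagnostic test with an AUC" set at 0.90, at two-sided 0.05 with a correlation of 0.6. It does not say which two tests are meant.

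**The concern.** A power of 80% and an error rate of 5% describe one contrast chosen in advance. The article fixes the comparator but not which of four QP CMR indices stands for QP CMR, nor which metric decides. With a blanket threshold, a significant result on any index, metric or reference standard can be called a difference between techniques.

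The Conclusions present the comparison as the study's novelty: "This is the first study comprehensively assessing and comparing head-to-head the diagnostic performance of a range of contrast- and non-contrast-based CMR imaging methods". They tie it to a validated workflow that may do without contrast. A chance difference on one of several indices or metrics could then be read as showing that one technique is better.

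**Working it through.** **Inputs from the protocol article.** Seven tests (Table 1); DeLong, McNemar and p<0.05 (2.9.2); 74/90 and 75/92 patients, AUC 0.81 and 0.90, two-sided 0.05, correlation 0.6 (2.9.1).

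**1. Reproducing the plan's power figures.** The Hanley–McNeil variance is V(A) = [A(1−A) + (m−1)(Q₁−A²) + (n−1)(Q₂−A²)]/(mn), with Q₁ = A/(2−A) and Q₂ = 2A²/(1+A).
- One AUC, 74/90: SE(0.81) = 0.0348 and SE(0.90) = 0.0259. Power = Φ[(0.09 − 1.96×0.0348)/0.0259] = 79.9%. The stated 80% reproduces.
- Two AUCs, 75/92: null variance 2V(0.81)(1−r); alternative variance V(0.81) + V(0.90) − 2r√[V(0.81)V(0.90)]. The article gives the correlation of the responses, not of the AUCs, so r is assumed to be 0.50, 0.55 or 0.60. Power is 76%, 81% and 85%. The stated 80% reproduces at r of about 0.55.

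Both figures are therefore sound for a single test at 0.05.

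**2. Counting contrasts.**
- New modalities against visual: 3 (QP CMR, ΔT1, OS-CMR).
- New markers against visual: 6 (four QP CMR indices, ΔT1, OS-CMR).
- All pairs of seven tests: 7×6/2 = 21.

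**3. Chance of at least one false AUC difference, large-sample check.** With equal true AUCs and equal correlations, this is the chance that the largest |difference|/SE in the set exceeds 1.96. It is 12.5% for 3 contrasts with a common comparator, 20.7% for 6, and 44.0% for all 21 pairs (studentized range, 7 groups). Treating tests as independent would give 1 − 0.95⁶ = 26% and 1 − 0.95²¹ = 66%. That overstates the risk, because the contrasts share tests and patients.

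**4. Simulation.** Seven equally accurate binormal tests, 74/90 patients, DeLong on AUCs, McNemar on sensitivity, specificity and accuracy at a common fixed cut-off. One set used AUC 0.81 with correlations 0.3 to 0.8, or 0.9 among QP indices (3,000 runs for AUC; 500 with McNemar added). Another used AUC 0.81 or 0.90 with correlations 0.3, 0.6, or 0.85 among QP indices and 0.4 elsewhere (1,500 runs). The three-contrast row comes from a further simulation at 74/90 and AUC 0.81 and from step 3.

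| Contrasts tested at p<0.05 | AUC only | AUC, sensitivity, specificity, accuracy |
|---|---|---|
| 3 modalities v visual | 12–13% | not run |
| 6 markers v visual | 14–21% | 31–39% |
| All 21 pairs | 38–46% | 65–71% |

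All figures are for FFR alone. Repeating the comparisons against iFR and Pd/Pa would raise them.

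**5. Power under possible remedies** (two-AUC formula, 74/90, r = 0.50 to 0.60).
- One named contrast at 0.05: 76–85%.
- Holm over three contrasts, at its strictest step (0.05/3 = 0.0167): 58–71%.
- Bonferroni over six (0.0083): 48–61%.
- Bonferroni over 21 (0.0024): 31–44%.

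**The case against.** The strongest reply has four parts.

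- **All-pairs testing is not stated.** A reader might infer from Table 1 that all 21 pairs will be tested, or multiply by four metrics and three reference standards to 252 tests. The article does not say so. The Abstract and Background name visual assessment as comparator, and section 2.9.2 speaks of modalities, of which the four QP CMR indices could be one. This stands. The three- and six-contrast figures fit the stated objective, and the 21-pair figures are an upper reading.
- **A false result is not shown to be likely.** It passes 50% only with all pairs over four metrics. This also stands.
- **The 182 does not rest on this comparison.** Section 2.9.1 sizes the study on the single-AUC test, and the 75+92 figure is a supporting check. This stands too.
- **Multiplicity for secondary endpoints usually belongs in the analysis plan, which is not shown.** This holds only in part. Silence on adjustment alone would be no finding. But the article does state a decision rule for all results and a power claim for a contrast it does not identify.

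**Conclusion.** The point holds in a limited form. The comparator is named, but the QP CMR index and the deciding metric are not, and one unadjusted threshold covers every comparison. On the narrowest reading, the chance of at least one false AUC difference is about 12–13%, some two and a half times the nominal 5%. For the six markers against visual it is 14–21% on AUC and 31–39% over four metrics. The higher figures (38–46% and 65–71%) apply only if all pairs are tested.

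The sizes assume equal true accuracy, binormal scores, a common fixed cut-off for McNemar and a visual score treated as continuous, although it is built from 0–4 segment grades. The ordering of the readings does not depend on the correlations tried.

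A reader might go further and doubt the primary result or the sample size. The documents do not support that: the QP CMR accuracy estimates and the 182 patients are untouched.

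**What to change.** In sections 2.9.1 and 2.9.2, name the contrast that the 75+92 calculation refers to: one named QP CMR index against the visual perfusion defect score, AUC by DeLong, FFR ≤0.80, two-sided 0.05.

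Report all other head-to-head comparisons as exploratory differences with 95% confidence intervals and no significance claim. These are ΔT1 and B-MORE against visual, the other QP CMR indices, the McNemar comparisons, and the iFR and Pd/Pa repeats.

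If confirmatory claims are wanted for ΔT1 and B-MORE against visual, apply Holm across the named contrasts. A fixed sequence starting with QP CMR suits less well, because it would make the contrast-free methods depend on QP CMR beating visual reading.

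The cost is a few sentences before the data are analysed, with no added patients or measurements. Comparisons outside the list can no longer be called significant. Holm lowers power per contrast, to 58–71% at its strictest step with three contrasts, against 76–85% for a single named contrast.
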